### Consent

Interested individuals will contact the study coordinator by telephone, upon which a pre-screening will be conducted to exclude participants based on the criteria above that can be determined over the phone. If the first criteria are met, a meeting will be scheduled to go through the consent and a secondary screening process will take place. Each participant will provide informed consent before the secondary screening process takes place. The study coordinator will again go through the exclusion and inclusion criteria to see if the participants are eligible for the study. Next, all study details will be outlined and the participants will be given a chance to ask any questions. If they consent to the study, the participant’s blood pressure will be measured six times within 10 to 15 minutes using a BPTru automated blood pressure machine BPTru, Coquitlam, BC, Canada to test if the participant has elevated blood pressure and meets the study criteria. The healthcare professional will also perform a brachial blood pressure measurement with a sphygmomanometer BPTru, Coquitlam, BC, Canada as is standard procedure at the doctors’ office. At this time, they will also see the lead medical doctor, [name], at the hypertension clinic at the Health Sciences Centre for an examination to exclude any macrovascular target organ damage. If the participants meet the inclusion and exclusion criteria they will be notified by telephone of their acceptance into the trial if they still choose to participate. Figure 1 details the study overview and design.

**Figure 1 F1:**
[figure not shown]
Study design overview.

### Randomization and interventions

Upon acceptance into the trial all participants will be provided information on lifestyle management of hypertension. These strategies include the dietary approaches to stop hypertension, limiting alcohol and salt intake, limiting or stopping cigarette smoking, increasing physical activity, and losing weight if the individual is overweight or obese. However, it is not mandatory to adopt these lifestyle changes to be eligible for the trial.

Immediately after the baseline assessments, subjects will be randomized to one of two possible groups by a non-restricted computer-generated randomization schedule. The allocation ratio will be 1:1. The study coordinator will enroll the participants and the individual in charge of food delivery will be in charge of participant allocation. The allocation order will be in sequential, opaque, sealed envelopes. At this point all those involved in the study will be blinded to the group allocation excluding the individual responsible for food delivery.

The participants will be provided either the control or flaxseed-containing food products such as muffins, bagels, snack bars, and milled seeds to consume once a day for six months. A variety of flavors will be provided to assure the participants do not tire of the foods. In addition, participants will be encouraged to remain in the study and be adherent by describing to them the importance of their contribution to identifying new treatment strategies for hypertension. The control food products will contain a combination of wheat, pecans, and/or mixed dietary oils to replace the flaxseed. This combination of ingredients for the control food product will and has allowed for the best concealment and ability for a blinded trial. The formulation and flavor profiling of the flaxseed food products has been previously published [10,11].

### Participant assessments

#### **
*Averaged automated blood pressure*
**

The primary outcome measure is blood pressure. Blood pressure will be measured at a total of five visits: screening, baseline, two, four, and six months. A BPTru machine will be utilized to measure blood pressure six times within 10 to 15 minutes. The first reading will be discarded and the remaining five will be averaged. This measurement will take place in a quiet room while the participant is in a seated position and arm rested on an arm rest at heart level. A blood pressure reading with a sphygmomanometer and stethoscope will also be performed to ensure the congruency between this measurement and the automated measurement.

#### **
*Need for anti-hypertensive medication*
**

One of the secondary outcome measures is the need for anti-hypertensive medication. In the first two months of the trial the participants will not be prescribed anti-hypertensive medication as this is the lifestyle intervention period. A meta-analysis published in 2008 concluded the administration of a placebo to patients with hypertension for four to eight weeks provided no objective reason against safety [12]. At two, four, and six months the participants will have a blood pressure follow-up. The participants will be assessed for the need for anti-hypertensive medication. If deemed necessary, they will be prescribed anti-hypertensive medication according to the Canadian Hypertension Education Program guidelines. If prescribed anti-hypertensive medication, the type and dose of anti-hypertensive medication will be recorded. If a follow-up visit is required sooner than the two-month interval, the patient will be asked to return to the clinic for more visits as standard of care.

#### **
*Anthropometrics and questionnaires*
**

The secondary outcome measures also include anthropometrics, food intake, and physical activity. At baseline, the participants will be asked to fast (9 to 12 hour overnight fast) for blood and urine collection. The blood and urine will be analyzed utilizing techniques including metabolomics and lipid profiling. Biological specimens will be coded with an anonymous patient code and locked in a -80°C freezer. Height, weight, and waist circumference will be measured and body mass index (BMI) will be calculated to assess if the intervention may cause any changes in weight or waist circumference. They will also be asked to fill out a 24-hour food recall form with the study coordinator using the multiple-pass method as established by the United States Department of Agriculture [13] and the standardized international physical activity questionnaire (short) [14]. These two surveys are used to assess the participants’ typical food intake and physical activity habits. These assessments will be repeated at two, four, and six months to assess any changes in diet or physical activity over time, as detailed in Figure 1.

#### **
*Biochemical analysis*
**

The secondary analysis will include the biochemical analysis of plasma or blood. Biochemical analysis also will be performed to determine potential anti-hypertensive mechanisms of action and adherence to intervention. Plasma samples from baseline, two, four, and six months will be analyzed for lipid profiles, metabolomics profile, and for any circulating plasma component that may influence blood pressure regulation. Plasma analysis of alpha-linolenic acid and enterolignans will act as adherence markers. Urine samples from baseline, two, four, and six months will also be analyzed for metabolomics profiling.

#### **
*Statistical analysis*
**

All data will be stored without identifiable participant information in a password protected electronic document or locked cabinet. The final trial data set will be accessible only to researchers involved in the trial and any medical review board that requires access for safety purposes. In the likelihood of an unbalanced data set, absolute values will be analyzed with a mixed two-way repeated measures model with group and time as the between and within factor, respectively. A *post-hoc* comparison of the least squared means with a Tukey’s adjustment will be utilized to determine where the specific differences lie. Absolute change will also be calculated only for participants who provide clinical information and samples at all time points. Absolute change can be analyzed with one way analysis of variance (ANOVA) and the Kruskal-Wallis test, or multiple *t*-tests and the Mann Whitney U test with a false discovery rate correction. Multiple regression may be used to determine the influence of flaxseed on blood pressure while including factors such as age, BMI, gender, diet, or physical activity. Correlations will be utilized to determine relationships between biochemical markers and blood pressure. Subgroup analyses may also be performed, for example, the dichotomization of change in biochemical markers and observing subsequent change in blood pressure. All statistical tests will be set at a significance level of 0.05. Data will be published in peer-reviewed journals and discussed in public forums such as radio and television broadcasts.

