**Methods/Design:**

The HYPERFlax Trial is a parallel, superiority, phase II/III, randomized, double-blinded, controlled clinical trial. St. Boniface Hospital and the Health Sciences Centre of Winnipeg, Canada, will recruit 100 participants newly diagnosed with stage 1 hypertension who have yet to be administered anti-hypertensive medication. Participants will be randomly allocated with a 1:1 ratio into a flaxseed or control group and provided food products to consume daily for six months. At baseline, two, four, and six months, participant assessments will include the primary outcome measure, averaged automated blood pressure, and secondary measures: 24-hour food recall, international physical activity questionnaire, anthropometrics, and blood and urine sampling for biochemical analysis. Plasma will be assessed for lipids, metabolomics profiling, and molecules that regulate vascular tone. Urine will be collected for metabolomics profiling. With an estimated dropout rate of 20%, the trial will have a power of 0.80 to detect differences between groups and across time, out of an effect size of 0.7 (SD) at an α level of 0.05.

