Despite the significant anti-hypertensive effects demonstrated in the FlaxPAD trial, the results contained some important limitations. Firstly, participants of the FlaxPAD trial were already on anti-hypertensive medication yet still exhibited poorly controlled blood pressure [8]. Therefore it is not possible to conclude if flaxseed can reduce blood pressure as a monotherapy or if it is only effective in conjunction with anti-hypertensive medication. Secondly, it remained unclear if flaxseed could effectively reduce blood pressure in hypertensive patients without coexisting peripheral arterial disease. Therefore, despite evidence showing the potential of flaxseed as a potent cardioprotective functional food, the efficacy of flaxseed as an independent treatment to reduce blood pressure in newly diagnosed patients with primary hypertension has yet to be investigated.

The hypothesis to be tested in the present study is: dietary flaxseed will reduce blood pressure in patients with newly diagnosed hypertension and will reduce the need for anti-hypertensive medication. In order to test these hypotheses, a phase II, randomized, double-blinded, controlled clinical trial called HYPERFlax has been designed. The acronym for the HYPERFlax trial stands for the anti-HYPERtensive effects of dietary Flaxseed. Parameters such as blood pressure, plasma and urine metabolomics, plasma lipid profiling, and plasma vascular tone regulators will be analyzed to assess the efficacy and mechanisms of action of dietary flaxseed in hypertension management.

The aims of the HYPERFlax trial are to:

1. determine if consuming 30 g of milled flaxseed daily can effectively reduce blood pressure over six months in newly diagnosed stage 1 primary hypertensive participants;

2. determine if dietary flaxseed is efficacious as a monotherapy;

3. determine if flaxseed can reduce the need for anti-hypertensive medication; and

4. identify the mechanisms of action responsible for the potential anti-hypertensive effects of flaxseed.

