### Settings and participants

The trial will take place at the Health Sciences Centre Hospital and St Boniface Hospital in Winnipeg (Manitoba, Canada). The aim is to enroll 100 participants. Based on the previous FlaxPAD trial [8] the expected attrition rate is 20%, which still allows for a power of 0.80 to detect differences between groups and across time, out of an effect size of 0.7 (SD) at an α level of 0.05. Participants will be recruited through doctor referral or in response to public advertisements and public screening booths. The inclusion and exclusion criteria below fit the criteria of individuals who are not recommended to be administered anti-hypertensive medication immediately according to the Canadian Hypertension Education Program Guidelines [9]. These individuals do not have a systolic or diastolic blood pressure of more than 160/100 mmHg and do not have diabetes or macrovascular target organ damage. The exclusion criteria, therefore, allow a period of time for lifestyle intervention, including new therapeutic strategies like dietary flaxseed, in low-risk hypertensive individuals.

Inclusion criteria includes:

1. stage 1 essential hypertension (average automated systolic blood pressure of 135 to 160 mmHg or diastolic blood pressure of 85 to 100 mmHg) [9];

2. Newly diagnosed; defined as being clinically diagnosed within the last six months. This includes being diagnosed at the screening examination;

3. Male or female;

4. Untreated by medications for hypertension;

5. 18 to 85-years-old and able to provide informed consent;

6. Females who are not pregnant and not planning on becoming pregnant during the course of the trial. A pregnancy test will not be administered for the trial;

7. Subjects who are receiving anti-platelet therapy must be on a stable dose for three months prior to the study;

8. Subjects who are receiving lipid-lowering drugs must be on a stable dose for three months prior to the study;

9. Subjects must have access to freezer space in their residence to hold up to one month of the frozen food products associated with this study.

Exclusion criteria includes:

1. Patients with ischemic pain at rest in limbs, ulceration, or gangrene.

2. Patient has undergone percutaneous coronary angioplasty, or has had coronary bypass within the last six months.

3. Known secondary hypertension of any etiology.

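### The primary outcome names neither systolic nor diastolic pressure, nor a deciding visit or model effect, so the false-claim rate can exceed 5%

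*Protocol article*

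**What the plan says.** Under Participant assessments, the article states "The primary outcome measure is blood pressure". The abstract is slightly fuller: "participant assessments will include the primary outcome measure, averaged automated blood pressure, and secondary measures". That settles how a reading is obtained, not which reading decides.

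- **Component.** Both are in use. Entry under Settings and participants is by "average automated systolic blood pressure of 135 to 160 mmHg or diastolic blood pressure of 85 to 100 mmHg".
- **Visit.** "Blood pressure will be measured at a total of five visits: screening, baseline, two, four, and six months", so there are three visits after baseline and none is called primary. Aim 1 in the Background asks whether flaxseed "can effectively reduce blood pressure over six months in newly diagnosed stage 1 primary hypertensive participants", which fits a six-month contrast, an average over visits or a group-by-time effect.
- **Model.** Under Statistical analysis, "absolute values will be analyzed with a mixed two-way repeated measures model with group and time as the between and within factor". Whether the group effect, the interaction or a contrast at one visit decides is not said.
- **Other analyses.** "Absolute change can be analyzed with one way analysis of variance (ANOVA) and the Kruskal-Wallis test", or alternatively with t-tests and the Mann-Whitney test under a false discovery rate correction. Multiple regression is optional.
- **Level.** "All statistical tests will be set at a significance level of 0.05".

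**The concern.** A superiority trial needs one identifiable comparison, or a stated family of comparisons, on which its claim rests. Here the outcome covers two components and three visits, and nothing says whether one positive result is enough or which one it must be. The choice could be made after the data are seen.

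The two named corrections do not close the gap. Tukey works on post-hoc means within one model, and systolic and diastolic pressure would be modelled separately. The false discovery rate correction follows the t-test and Mann-Whitney option, and its family is not defined. The ANOVA and Kruskal-Wallis option has no correction clearly attached to it.

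At stake is whether a positive report of lower blood pressure carries the 5% error that a reader would assume.

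**Working it through.** **Inputs from the article.** 100 enrolled, 1:1 allocation, 20% attrition, effect 0.7 SD, alpha 0.05, stated power 0.80; two components; three follow-up visits.

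**Assumptions, not in the article.** Two-sided tests, complete data in 40 per arm, and correlations of 0.5-0.7 between systolic and diastolic and between visits.

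**1. The plan's own power figure.** 100 × 0.8 = 80, or 40 per arm.

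- Power at 0.05 = Φ(0.7·√(40/2) − 1.960) = Φ(3.130 − 1.960) = Φ(1.170) = 0.88 (0.87 with the t distribution). The stated 0.80 is not reproduced; it is conservative.
- Per arm for 0.80: 2(1.960 + 0.842)²/0.7² = 32.04, so 33; enrolled 66/0.8 = 82.5, so 83.
- Power at 0.025 = Φ(3.130 − 2.241) = Φ(0.889) = 0.81 (0.80 with t). Per arm: 2(2.241 + 0.842)²/0.7² = 38.8, so 39; enrolled 78/0.8 = 97.5, so 98. The article does not mention this level.

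**2. Upper bounds if the tests were independent.** 1 − 0.95^k gives 9.8% for k = 2, 14.3% for k = 3 and 26.5% for k = 6.

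**3. Either component at one visit.** 1 − P(|Z₁| ≤ 1.96 and |Z₂| ≤ 1.96), bivariate normal: 9.1% at correlation 0.5 and 8.3% at 0.7.

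**4. All six component-by-visit tests, and the named corrections.** Two null simulations were run:

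- (a) six normal test statistics, with component and visit correlations multiplied, 400,000 draws per setting;
- (b) patient-level data, 40 per arm, baseline and three visits, 10,000 trials per setting, with tests on change from baseline where change is used.

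| What may carry the claim | (a) | (b) |
|---|---|---|
| Any of six tests, uncorrected | 17.7-21.8% | 20.1-22.3% |
| False discovery rate over visits within each component, either component | 7.3-8.5% | 7.7-8.4% |
| False discovery rate over all six | 4.0-4.6% | 4.2-4.9% |
| Group-by-time interaction, either component | – | 8.6-8.9% |
| Group effect or interaction, either component | – | 16.0-17.1% |
| Tukey-adjusted between-group visit contrasts only, either component | – | about 1% |

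Raising the systolic-diastolic correlation to 0.8 lowers the figures only slightly: either component at one visit becomes 7.8%, and six uncorrected tests in (b) about 19%.

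**The case against.** The strongest reply has three parts.

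**The plan has a hierarchy and corrections.** The mixed model is the only analysis firmly committed to. Change scores come in addition, only for participants with data at all time points, and regression is optional. Two corrections are named, and the wording leaves open whether the false discovery rate covers both change-score options. This stands. A reader might infer that all these analyses are equal rivals, each at an uncorrected 0.05, and that the error rate is therefore about 20%. The article does not support that. The 18-22% figure requires the optional change-score tests to decide, no correction to apply and any of six results to count.

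**Detail of this kind belongs in an analysis plan.** For the choice between a parametric and a rank test, and for labelling supportive analyses, that is fair, and neither counts as a defect here. It does not excuse leaving out the component and the deciding contrast, because these define what the trial tests.

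**The power statement shows one intended test at 0.05.** A reader might infer this, but the statement refers to differences between groups and across time and names no test. Its 0.80 is not what a single two-sided 0.05 test gives with 40 per arm. It supports no conclusion about the number of tests intended.

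**Conclusion.** The concern holds in a limited form. The article names neither the component, nor the deciding visit, nor the deciding model effect, and neither stated correction is said to cover systolic versus diastolic. The false-claim rate is therefore not fixed at 5% and can exceed it.

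The core size is about 8-9%, from systolic versus diastolic at one visit. Crediting the false discovery rate within each component leaves about 7-9%. The extreme of 18-22% needs all six tests open and uncorrected. The rate stays at or below 5% if the false discovery rate spans all six tests, or if only Tukey-adjusted visit contrasts decide, but the article commits to neither.

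These figures rest on the assumed correlations, two-sided testing and complete data. The point should be corrected. It does not show that the trial is too small.

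**What to change.** Before unblinding, name one deciding contrast from the mixed model already committed to. One example is the flaxseed-minus-control difference in averaged automated systolic pressure at six months, tested two-sided at 0.05. Then choose one rule for diastolic pressure:

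- **Fixed sequence:** test diastolic at the same visit at 0.05 only if systolic is significant. Power for systolic is about 0.87 with 40 per arm and 0.7 SD.
- **Split alpha:** let either component carry the claim, each at 0.025. The family error is at most 5%, and power is about 0.80 for a component with a true effect of 0.7 SD.

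Label the other visits, the change-score tests and the regression as supportive.

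Anti-hypertensive medication may be prescribed from the two-month visit, and one aim concerns monotherapy. The plan should therefore state how the analysis treats readings taken after such medication has started. This takes a real decision about what is being estimated, beyond the naming of an endpoint.

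Cost: protocol text and that decision; 100 participants remain enough under either rule. Under the fixed sequence, a positive diastolic result cannot carry the claim if systolic fails, which matters because participants may enter on diastolic pressure alone. Splitting alpha avoids that at the price of power falling from about 0.87 to 0.80.

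### Two pre-randomisation blood pressures exist for every participant, but no analysis named in the article uses either as a covariate: an optional gain in precision, mostly from the baseline value

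*Protocol article*

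**What the plan says.** - Measurement (Participant assessments, Averaged automated blood pressure): "Blood pressure will be measured at a total of five visits: screening, baseline, two, four, and six months". One method is described: six automated readings, the first dropped and the other five averaged. The Consent section confirms that at screening "blood pressure will be measured six times within 10 to 15 minutes using a BPTru automated blood pressure machine".
- Timing (Randomization and interventions): allocation comes directly after the baseline assessments, so screening and baseline both precede it. "The allocation ratio will be 1:1".
- Stated role of screening: eligibility only (Settings and participants; Consent). The Abstract lists the primary outcome at baseline, two, four and six months, without screening.
- Analysis (Statistical analysis): a mixed repeated measures model on absolute values with group and time; absolute change in participants with data at all time points; and a possible multiple regression "while including factors such as age, BMI, gender, diet, or physical activity". No pre-randomisation pressure is named as a covariate. The levels of time are not listed.
- Size (Settings and participants): "The aim is to enroll 100 participants"; "the expected attrition rate is 20%, which still allows for a power of 0.80", "out of an effect size of 0.7 (SD) at an α level of 0.05". The Statistical analysis section adds "All statistical tests will be set at a significance level of 0.05". No SD in mmHg and no correlation between visits is given.

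**The concern.** A participant's own earlier pressure is usually the best available predictor of later pressure. Adjusting for it removes between-person variation from the comparison of flaxseed with control, and corrects chance imbalance, which unrestricted randomisation leaves possible. A single visit carries visit-to-visit noise, so a second pre-randomisation visit can add information that the first does not hold. Here both values are already collected by the same method, and the screening value is complete because nobody enters without it. Both precede allocation, so adjusting for them does not bias the comparison. What is at stake is the width of the confidence interval in a trial expected to finish with about 80 people, not the validity of the result.

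**Working it through.** **Inputs.** From the article: 100 enrolled, 20% attrition (80 completers, 40 per arm), 0.7 SD, alpha 0.05, and an entry window at screening of systolic 135-160 or diastolic 85-100 mmHg. Assumed, because the article is silent: a two-sided test; visit correlation r of 0.5 to 0.8; screened-population systolic mean 135-145 and SD 10-15 mmHg, diastolic mean 86 and SD 10; systolic-diastolic correlation 0.6. The 0.7 is read as a multiple of the SD of follow-up pressure.

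**1. The plan's own power figure.** Power = Φ(d√(n/2) − 1.96), and 0.7 × √20 = 3.130. Φ(3.130 − 1.96) = Φ(1.170) = 0.879; the t-test gives 0.871. The stated 0.80 is not reproduced and is conservative: 0.80 needs about 33 per arm.

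**2. No range restriction.** With k equally correlated pre-randomisation values as covariates, residual variance relative to a comparison of follow-up levels is 1 − k·r²/(1 + (k−1)r).

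| r | baseline only | baseline + screening | ratio |
|---|---|---|---|
| 0.5 | 0.75 | 0.667 | 0.889 |
| 0.6 | 0.64 | 0.550 | 0.859 |
| 0.7 | 0.51 | 0.424 | 0.830 |
| 0.8 | 0.36 | 0.289 | 0.802 |

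Absolute change has relative variance 2(1−r), that is 1.0, 0.8, 0.6 and 0.4. Baseline as a covariate is better at each r.

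**3. With the entry rule.** Screening is the selection reading, so its range is cut and it predicts less. Simulation with 2,000,000 draws per scenario, truncating screening either on systolic alone or on the either-pressure rule, gave:

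| r | cut from baseline | further cut from screening, systolic-only rule | further cut, either-pressure rule |
|---|---|---|---|
| 0.5 | 14-18% | 3-5% | 5-7% |
| 0.6 | 19-26% | 4-7% | 8-9% |
| 0.7 | 26-36% | 6-10% | 10-12% |
| 0.8 | 35-50% | 9-13% | 14-15% |

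The overall further cut is about 3-15%. Interval width scales with the square root: √0.97 = 0.985 and √0.85 = 0.922, so intervals are about 1.5% to 8% narrower.

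**4. If screening predicts follow-up less well than baseline does.** Without truncation, the further cut is (c − r²)²/(1 − r²)², where c is the screening-to-follow-up correlation and the other correlations stay at r. At r = 0.6 and c = 0.5: 0.14²/0.64² = 4.8%. At r = 0.8 and c = 0.65: 0.01²/0.36² = 0.1%. With truncation under the either-pressure rule (assumed screened means 138/86, SD 15/10), lowering c by 0.10 leaves 2.6% (r = 0.6), 2.8% (0.7) or 1.9% (0.8). Lowering it by 0.15 leaves about 1% at r = 0.6 and 0.7. With first-order decay (c = r²) nothing is left.

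**5. Power at 0.7 SD, 40 per arm.** Take r = 0.6, systolic mean 135, SD 15, either-pressure rule: relative variance is 0.741 with baseline and 0.676 with both. Φ(3.130/√0.741 − 1.96) = 0.953 and Φ(3.130/√0.676 − 1.96) = 0.968, a gain of 1.5 points. Across all scenarios in step 3, power is 0.92-0.99 with baseline only and 0.93-0.998 with both. No scenario gains more than about 1.5 points.

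**The case against.** The strongest case against raising this is that nothing in the article is wrong. Using an eligibility reading for eligibility is ordinary practice, and the choice of covariates is commonly left to an analysis plan, which is not shown. This stands, and it is why the point is put as an optional improvement.

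A reader might infer that no analysis in the trial uses the screening value. The article does not support that. It is condensed, its covariate list is open-ended, and the levels of time are not given. It supports only that no analysis it names uses either value as a covariate. The Abstract makes it likelier that screening is not an outcome visit, but says nothing about covariates. If screening were one more level of time in an unconstrained group-by-time model, the precision would not be recovered and a group main effect would be diluted.

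A reader might also start from the stated power of 0.80 and conclude that screening lifts it to 0.82-0.86. That needs a starting effect of about 0.634 SD, which is not the trial's. At 0.7 SD, power is already about 0.87-0.88 before any adjustment.

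A third objection is that screening may predict follow-up less well than baseline does. The interval between the two visits is not stated, lifestyle information is given on acceptance, a four-week washout may precede entry, and for some people screening is the diagnostic visit. This also stands, and it is why the range reaches zero. It affects the size of the gain only, because a value that precedes allocation does not bias the comparison.

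Finally, baseline is not ignored altogether: absolute change uses it by subtraction. That is a less efficient use than a covariate (step 2), and it is confined to participants with data at all time points.

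**Conclusion.** The point holds as a modest efficiency gain. Two averages of the primary outcome precede randomisation in every participant, and no named analysis adjusts for either. Measured against a comparison of follow-up levels, most of the gain comes from baseline: about 14-50% of variance over the assumed correlations. Screening adds about 3-15% if it predicts follow-up as well as baseline does, and 0-3% if its correlation with follow-up is 0.10-0.15 lower. Its added power is at most about 1.5 points, so its value lies in slightly narrower intervals. At the bottom of the range, the degree of freedom it uses, worth roughly one percentage point with about 80 completers, can cancel the gain.

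All correlations, means and SDs are assumptions. The power bound also depends on reading 0.7 SD in units of follow-up pressure; if it already meant a baseline-adjusted SD, the gain in power would be larger. Nothing here shows the trial to be underpowered or its planned comparison to be biased.

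**What to change.** In the Statistical analysis section, prespecify that the between-arm comparison at two, four and six months includes the baseline averaged automated pressure as a covariate and, alongside it, the screening averaged automated pressure: systolic values in the systolic model, diastolic values in the diastolic model. State that screening is not an outcome visit, since it is truncated by the entry rule. Keep the unadjusted result as a sensitivity analysis. Settle this before unblinding, because covariates added afterwards are open to challenge.

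The cost is one sentence in the plan and one degree of freedom for screening beyond the one for baseline. No new visits, data or participants are needed. If only one covariate is adopted, it should be baseline.
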